### Group Classification

1.5

MCI with 22 < MoCA < 26 or 20 < MMSE < 24 after 2 weeks of intervention and post‐assessments will be divided into two groups (score post‐intervention > score pre intervention = responder, according to MCID threshold (i.e., an increase of at least 3 points or 10% on the MMSE, or an increase of at least 1 point on the MoCA); score post‐intervention ≤ score pre‐intervention = non‐responder).

### Endpoint Measures

1.6

#### Primary Endpoint

1.6.1

The primary endpoint is the proportion of responders according to MCID. Additionally, the primary analysis will determine which cognitive subdomains show the greatest therapeutic effects.

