#### Questionnaire

1.2.1

The most popular test for diagnosing dementia is the MMSE, whereas the Montreal Cognitive Assessment (MoCA) is a very accurate test for mild cognitive impairment. To assess volunteers' global cognition, we will use MMSE and MoCA.

Thirty questions make up the MMSE, which evaluates orientation (10 points), immediate recall (3 points), attention and calculation (5 points), recall (3 points), and language (9 points) (Seyedian et al. 2008; Abe et al. 2020).

Eight cognitive domains are evaluated by the thirty questions in the MoCA, which also include executive functions and visuospatial skills (5 points), attention (6 points), naming (3 points), abstract thinking (2 points) language (3 points), recall (5 points), and orientation (6 points) (Badrkhahan et al. 2020). Higher scores on the MMSE and MoCA indicate higher cognitive function; scores range from 0 to 30. Because of the nature of questionnaires, if participants are uneducated (0 year of schooling), we add 3 points to the score of MMSE. Range of the Farsi version of thr MMSE is 20 < MMSE < 24, indicating MCI (Delbari et al. 2024). Besides, in MOCA test, Because the nature of questionnaires, if the subjects have less than 12 years of schooling (1‐11 years of schooling), we add 1 point to the score and range of 22 < MoCA < 26 indicate MCI (Zhao et al. 2011). For educated individuals, we will use MOCA exams. and for uneducated subjects (0 years of schooling), we will only use the MMSE test.

Finally, a history and mental state assessment by a psychiatrist based on the Diagnostic and Statistical Manual of Mental Disorders, fifth edition (DSM‐V), is crucial because the decline or stability of cognitive performance compared to the past is the most important issue (Edition 2013; Kaplan 2015).

MMSE and MoCA tests will be repeated at the end of the treatment to classify participants as responders or non‐responders to the intervention. We will use the minimal clinically important difference (MCID), based on clinically meaningful changes in cognitive test scores. The MCID denotes the smallest change in score perceived as beneficial or significant by patients or clinicians. Detailed thresholds for the MMSE and MoCA tests are comprehensively described in the post‐intervention assessment section.

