#### Primary Endpoint

1.7.1

All assessors will be blinded to group allocation and receive data labeled as “group A” and “group B.” Statistical analyses will be conducted using StataNow18.5 (Stata Corp, College Station, TX, USA), adhering to CONSORT guidelines. Normality of continuous variables will be checked using skewness and kurtosis, with variables considered non‐normal if absolute skewness > 2 or kurtosis > 3. Baseline characteristics, including (sex, hyper‐lipidemia, hypothyroid, hyper‐tension, diabetes, smoking, ischemic heart disease, education, and age) will be compared between groups using Fisher's exact test for categorical variables and the Mann–Whitney *U* test for non‐normal continuous variables. For normally distributed continuous variables, between‐group comparisons will be performed using the independent samples t‐test.

Initially, paired *t*‐tests (a suitable transformation or non‐parametric test) or equivalents for non‐normal data will be used to evaluate overall pre‐ to post‐rTMS changes within all 25 participants, assessing global treatment efficacy and identifying cognitive subdomains demonstrating the greatest response. Subsequently, participants will be categorized into responders and non‐responders based on MCID criteria. Between‐group comparisons of cognitive scores and subdomains will then be performed using ANOVA for baseline and ANCOVA for post‐intervention outcomes, adjusting for baseline scores and potential confounders. Pre‐intervention values refer specifically to baseline cognitive test scores, totally and in each cognitive sub‐domain, and related continuous variables measured before rTMS, which serve as covariates in the analyses. The QEEG features are analyzed separately as part of the secondary endpoint assessment. For non‐normal variables, suitable transformation will be applied, and median differences with percentage changes reported. Marginal plots from ANCOVA will visualize adjusted group differences post‐intervention. This two‐stage analytical approach allows comprehensive evaluation of rTMS effects both globally and within clinically meaningful responder groups across cognitive domains.

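### The primary analysis is told to pick the best-responding cognitive subdomain after the data are seen, in a study that otherwise calls itself exploratory

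*Protocol article*

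**What the plan says.** Section 1.6.1 of the protocol article opens with one endpoint: "The primary endpoint is the proportion of responders according to MCID". The next sentence widens the task: "Additionally, the primary analysis will determine which cognitive subdomains show the greatest therapeutic effects".

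Section 1.7.1, the statistical methods for the primary endpoint, puts this into practice. Paired t-tests, or equivalents for non-normal data, are run before against after rTMS in all 25 participants, "assessing global treatment efficacy and identifying cognitive subdomains demonstrating the greatest response". A second layer on the same scores follows once participants are split by response: "Between‐group comparisons of cognitive scores and subdomains will then be performed using ANOVA for baseline and ANCOVA for post‐intervention outcomes".

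Section 1.2.1 shows how many subdomains there are. For the MoCA it itemises "executive functions and visuospatial skills (5 points), attention (6 points), naming (3 points), abstract thinking (2 points) language (3 points), recall (5 points), and orientation", which makes seven blocks, although the same sentence speaks of eight domains. For the MMSE it itemises "orientation (10 points), immediate recall (3 points), attention and calculation (5 points), recall (3 points), and language (9 points"), which makes five. Schooled participants take the MoCA and unschooled participants take only the MMSE (sections 1.2.1 and 1.4.1).

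The article states no significance level, singles out no subdomain and gives no order of testing. The last paragraph of the introduction calls the study an exploratory pilot. Section 4 says that the small sample rules out definitive hypothesis testing.

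**The concern.** The added sentence in 1.6.1 gives the primary analysis a second job: to find the best subdomain among several, using the same data that will then be quoted as evidence for it. This goes beyond a missing multiplicity rule. The article itself states the data-driven choice and places it under the primary label.

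Two things are at stake. First, a subdomain could be presented as a primary rTMS effect because it happened to come out on top. Second, the largest of several noisy estimates is biased upward. The introduction and section 4 both say that the pilot's effect sizes should inform the design of later trials, so an inflated subdomain effect could pass into their planning.

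**Working it through.** The plan has no figure of its own to reproduce: it gives no alpha, power or error rate for these tests.

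**Inputs from the article**
- 25 participants in a single arm (abstract, section 1.7.1).
- Seven itemised MoCA blocks and five MMSE blocks (section 1.2.1).

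**Assumptions, because the article gives no figure**
- Two-sided 0.05 per test, unadjusted.
- All 25 participants on the MoCA. The split between instruments is unknown.
- Normally distributed changes, equally correlated between blocks, with correlation from 0 to 0.8.

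**Step 1: chance of a false subdomain finding when nothing changes**

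For k independent tests the chance of at least one significant result is 1 − (1 − a)^k. Significant improvement uses only the favourable tail, a = 0.025. A change in either direction uses a = 0.05.

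- Seven MoCA blocks, improvement: 1 − 0.975^7 = 0.162.
- Seven MoCA blocks, either direction: 1 − 0.95^7 = 0.302.
- Five MMSE blocks, improvement: 1 − 0.975^5 = 0.119.
- Five MMSE blocks, either direction: 1 − 0.95^5 = 0.226.

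Positive correlation between blocks lowers these rates. Simulated paired t-tests with n = 25 and seven blocks give:

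| Correlation | Improvement | Either direction |
|---|---|---|
| 0 | 16% | 30% |
| 0.5 | 12% | 23% |
| 0.8 | 8% | 15% |

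One test chosen in advance would show a false improvement in 2.5% of trials. The search raises this to between 8/2.5 = 3.2 and 16/2.5 = 6.4 times that rate. A simulation with discrete, bounded scores like those of the MoCA, without correlation between blocks, gave the same rates as the normal model: 16% and 30%.

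**Step 2: overstatement of the winning change (no alpha needed)**

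Measure change in units of the SD of individual change. The standard error of a block mean is then 1/√25 = 0.2. The expected largest of seven independent standard normal values is 1.352. With common correlation r, the largest of seven equal true changes is overstated on average by 1.352 × 0.2 × √(1 − r).

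- r = 0.2: 1.352 × 0.2 × 0.894 = 0.24 SD.
- r = 0.5: 1.352 × 0.2 × 0.707 = 0.19 SD.
- r = 0.8: 1.352 × 0.2 × 0.447 = 0.12 SD.

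So with no true change in any block, the largest observed change averages +0.19 SD at r = 0.5. With an illustrative true change of 0.3 SD in every block, the apparent winner averages 0.30 + 0.24 = 0.54 SD at r = 0.2, 0.30 + 0.19 = 0.49 SD at r = 0.5, and 0.30 + 0.12 = 0.42 SD at r = 0.8. If fewer than 25 take the MoCA, the standard error grows and so does the overstatement.

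**Step 3: after the fix**

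With a Bonferroni level of 0.05/7, the chance of any significant result among seven independent tests is 1 − (1 − 0.05/7)^7 = 0.049. In simulations over correlation 0 to 0.7 it was about 3% to 5%. Holm controls the same error rate.

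**The case against.** The best defence is that the study declares itself an exploratory pilot, disclaims definitive testing and names a single primary endpoint. The abstract gives that endpoint without mentioning subdomains. On this view no confirmatory error rate exists to be inflated, and the choice of multiplicity procedure may sit in an analysis plan that is not shown.

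Much of this stands. The absence of an adjustment rule is not counted against the article. What remains is a sentence that the article does contain, and it assigns the choice of winner to the primary analysis. An unseen plan that adjusted p-values would leave both that label and the selection bias of step 2 in place.

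A reader might infer more than the text supports:
- *That a responding subdomain would appear by chance in up to 30% of trials.* That rate counts significant worsening. The article speaks of therapeutic effects and response, which mean improvement, so the ceiling for seven blocks is about 16%.
- *That the plan tests each subdomain at full alpha and would report any below 0.05 as a primary effect.* It states no alpha and no such rule, and the greatest response could be a plain ranking of estimates.
- *That the trial has no deciding endpoint.* The responder proportion is named, although section 1.7.1 attaches no test or null value to it.
- *That the MoCA and MMSE blocks form one family of 12 tests with 25 people each.* The instruments go to different participants. For the same reason, one total-score test across everybody is undefined.
- *That a winning subdomain will be used to plan a later trial.* The introduction links effect sizes mainly to QEEG, so this is a risk and not a stated intention.

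**Conclusion.** The point holds as a labelling and selection problem. A data-driven pick of the best subdomain stands inside the primary analysis, which conflicts with the study's own exploratory status. It does not show that a confirmatory claim has been inflated.

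The false-improvement rates of 8% to 16% depend on the assumed two-sided 0.05, on 25 participants on one instrument and on the range of correlation. The overstatement needs no alpha, but its 0.3 SD starting value is only an illustration. The sponsor should correct this. The change is cheap and leaves the responder endpoint untouched.

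**What to change.** 1. In section 1.6.1, delete the sentence that begins with *Additionally*, so that the responder proportion stands alone as primary.
2. In section 1.7.1, replace the clause on identifying the subdomains with the greatest response by *describing change in each subdomain*, and label this analysis exploratory.
3. Report every block of each instrument (seven MoCA, five MMSE, each in its own participants) with mean change and 95% confidence interval.
4. Either Holm-adjust the p-values within each instrument or state that none is confirmatory.
5. State that the largest observed subdomain change will not be used unadjusted as a planning effect size.

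The cost is wording in two sections and, if adjustment is chosen, one step in the analysis code. No new data are needed. The downside is that fewer subdomain results can be called significant.

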#### Eligibility Criteria

1.1.2

Inclusion criteria: (1) Persian language. (2) have the ability to visit the hospital. (3) all patients aged 60 years or older. (4) participants will be diagnosed with MCI in the Diagnostic and Statistical Manual of Mental Disorders‐5th edition (DSM‐V) and will be additionally assessed by the Montreal Cognitive Assessment (MoCA) (Badrkhahan et al. 2020) and the Mini‐Mental State Examination (MMSE) (Seyedian et al. 2008; Delbari et al. 2024) “22<MoCA<26 or 20<MMSE<24.” (5) not using of psychiatric or neurological medications. (6) patients who will sign informed consent forms.

Exclusion criteria: (1) a history of severe psychiatric problems such as a major depressive disorder or psychosis. (2) history of any neurostimulation treatments during the past 3 months. (3) contraindications to rTMS intervention, such as the presence of a cardiac pacemaker and ferromagnetic implants in the head or neck. (4) history of serious neurological illnesses, including epilepsy, seizures, or stroke. (5) abusing drugs or alcohol excessively. (6) with a skull fracture or craniotomy.

Patients diagnosed with MCI will be invited for EEG recording the next day. After EEG recording, those who consent to rTMS intervention will complete a screening questionnaire, supervised by a psychiatrist, prior to the treatment. The participants will all be eligible for TMS operation (Rossi et al. 2009; Mokhtarinejad et al. 2024) based on their responses to a TMS safety screening questionnaire. The TMS Safety Screening Questionnaire will be used to evaluate the eligibility for TMS intervention based on the questionnaire from Rossi et al. (2021), covering questions about the existence of risk factors, such as epilepsy or the presence of a cardiac pacemaker and ferromagnetic implants in the head or neck. According to their responses, patients will be categorized as either “Eligible,” or “Not eligible.”

Then complete an Iranian version of the 28‐item General Health Questionnaire (GHQ) (Ebrahimi et al. 2007). The General Health Questionnaire (GHQ‐28) is a general health screening tool, and obtaining a score of 24 (Ebrahimi et al. 2007) or higher is a condition for volunteers to continue participating in the study, as well as not having any TMS contraindications.

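### Comparing MoCA blocks on uncontrolled pre-post change is confounded with the room each block has to improve, so it cannot by itself identify the subdomain with the greatest therapeutic effect

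*Protocol article*

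**What the plan says.** Section 1.6.1 of the protocol article defines the primary endpoint as the proportion of responders and then adds that "the primary analysis will determine which cognitive subdomains show the greatest therapeutic effects". Section 1.7.1 gives the method: paired t-tests or non-parametric equivalents of pre- to post-rTMS change in all 25 participants, "identifying cognitive subdomains demonstrating the greatest response". It names no metric for comparing subdomains. For non-normal variables it asks for median differences and percentage changes. Baseline scores enter as covariates only in the later responder versus non-responder ANCOVA.

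Eligibility (section 1.1.2) is "22<MoCA<26 or 20<MMSE<24". Section 1.2.1 adds one point to the MoCA for 1 to 11 years of schooling. It lists the MoCA blocks as "executive functions and visuospatial skills (5 points), attention (6 points") and "naming (3 points), abstract thinking (2 points) language (3 points), recall (5 points), and orientation (6 points"), and states that "scores range from 0 to 30". Participants with no schooling are tested on the MMSE only, with three points added.

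The Discussion concedes treatment expectation in an open-label trial, and the Limitations section concedes small numbers. Neither mentions ceiling or unequal room to improve.

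**The concern.** The eligibility window limits how many points a MoCA patient can have lost, and the blocks differ in size. A block at its maximum cannot improve, and one that is a single point short can gain at most one point. A block with several lost points can show a larger change even if rTMS acts equally on every domain. The step that is meant to find the most responsive subdomain makes no allowance for this.

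At stake is a conclusion attached to the primary analysis. The trial could report a domain-selective benefit that equal action on all domains would also produce, and could call a block unresponsive when it had little room to move. The responder proportion is not affected.

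**Working it through.** **1. The article's own total.** The MoCA block maxima sum to 5 + 6 + 3 + 2 + 3 + 5 + 6 = 30, which agrees with the stated range.

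**2. Room per patient.** The window admits 23, 24 or 25.
- 12 or more years of schooling: 30 − 25 = 5 to 30 − 23 = 7 points lost.
- 1 to 11 years: the added point makes the raw score 22 to 24, so 6 to 8 points lost.
- Mean room per block: 5/7 = 0.71 to 8/7 = 1.14 points.

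**3. Blocks within one point of maximum.** If *L* points are lost, at most floor(*L*/2) blocks can be two or more points short, so at least 7 − floor(*L*/2) are at or within one point of maximum. The averages assume that items are lost at random.

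| Points lost | Guaranteed within 1 point | Average within 1 point | Average exactly at maximum |
|---|---|---|---|
| 5 | 5 of 7 | 6.0 | 3.2 |
| 6 | 4 of 7 | 5.6 | 2.7 |
| 7 | 4 of 7 | 5.2 | 2.3 |
| 8 (raw 22) | 3 of 7 | 4.8 | 1.9 |

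**4. What this does to a comparison of blocks.** The inputs here are assumptions, not figures from the article: 25 MoCA patients, scores 23 to 25 equally likely, each lost point regained with probability 0.25, each held point lost with probability 0.03, and three ways of spreading the deficit. In the last three columns one block has 2.4 times the effect (0.25 × 2.4 = 0.60).

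| Deficit profile | Mean points lost: recall / naming | Equal effects: block with most room has largest gain | Attention truly best: first on raw gain | Naming truly best: first on raw gain | Naming truly best: first on gain ÷ room |
|---|---|---|---|---|---|
| Items lost at random | 1.00 / 0.60 | 37% | 96% | 52% | 84% |
| Moderately recall/executive | 2.38 / 0.22 | 89% | 29% | 0% | 44% |
| Recall-dominant | 3.57 / 0.09 | about 100% | 0% | 0% | 18% |

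By chance the block with most room would be first in 1/7 = 14% of trials.

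**5. Does another metric help?** A second simulation assumed baseline success rates of 0.75 (visuospatial/executive), 0.85 (attention), 0.95 (naming), 0.75 (abstraction), 0.80 (language), 0.50 (recall) and 0.95 (orientation), with 25% recovery of lost points in every block. Recall ranks first in about 95% of trials on raw gain, 90% on the paired t-statistic and 97% on percentage change. With recall success raised to 0.60 and a 2% chance of losing each held point, the figures are about 85%, 76% and 82%. With a flat 0.80 in all blocks, percentage change instead favours the smallest block: abstraction is first in about 20% of trials.

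Gain divided by room is not a clean ranking either. In the random-loss case of step 4 with equal effects, it puts abstraction (2 points) first in 22% of trials and orientation (6 points) first in 8%, because small blocks are noisier.

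**6. MMSE participants.** The eligible range of 21 to 23 includes three added points, so raw scores are 18 to 20 and 10 to 12 points are lost. Over five blocks (10 + 3 + 5 + 3 + 9 = 30) that is 2.0 to 2.4 per block. The near-ceiling argument does not carry over.

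**The case against.** The plan does not say that subdomains are ranked by raw points. The metric is open, and an analysis plan that is not shown may settle it. That is correct, and the point should not be put as a criticism of a raw-point ranking. It does not rescue the claim, because the metrics that section 1.7.1 suggests (paired test statistic, percentage change) also give a winner that depends on room or block size when the true effect is equal.

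A reader might infer that the comparison measures room and nothing else, or that recall is bound to be named. The documents support neither. If points are lost evenly, the block with most room leads in only 37% of trials, and a large true effect in attention comes first in 96%. The dominance of recall rests on assumed success rates. A reader might also infer that most blocks are at full ceiling. That is not guaranteed, since seven lost points can fall one per block, and one lost point in abstraction is half its scale.

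It can also be said that equal effect was defined here as an equal share of lost points regained, which ties point gain to room. This is a choice. On a pure point scale the block that regains most points does have the largest gain. But the plan speaks of therapeutic effects, and unequal room is a competing explanation for unequal gain.

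Finally, the aim is secondary in weight: it is an addition to the responder proportion, in a pilot that calls itself exploratory and says it cannot support definitive hypothesis testing. Lack of a control already prevents attribution to rTMS. This limits the seriousness. It also fits poorly with wording that promises a determination.

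**Conclusion.** The concern holds for MoCA participants. The article's own window and block sizes put at least 4 of 7 blocks (3 of 7 at raw 22) within one point of maximum in every such patient. This bound needs no assumption. A comparison of blocks on uncontrolled pre-post change is therefore confounded with available room and cannot by itself identify the greatest therapeutic effect. Neither the pre-post analysis nor the stated limitations deal with this.

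The size is uncertain. With equal true effects, the block with most room has the largest gain in about 37% to nearly 100% of trials. That range comes from assumed deficit profiles and recovery rates, and from treating all 25 participants as MoCA-tested. The article gives neither the baseline profile nor the split between MoCA and MMSE. The point concerns what the trial may conclude about subdomains; the responder proportion and the QEEG comparison are not in question.

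**What to change.** In sections 1.6.1 and 1.7.1, replace "the primary analysis will determine which cognitive subdomains show the greatest therapeutic effects" and "identifying cognitive subdomains demonstrating the greatest response" with a descriptive aim. For each block, with MoCA and MMSE kept separate, report the number of patients at maximum at baseline, the points available, the change, and the gain as a share of available points with a 95% confidence interval. Name no most responsive domain on any of these metrics, including the share of available points.

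The cost is a change of wording and one descriptive table built from the block scores that the subdomain analysis already needs. The downside is that the claim to identify the most responsive domain is given up. Share-of-room estimates will also be imprecise for blocks where few patients start below maximum.
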